### Active and Passive Case Detection of Malaria

*Active case detection* is represented by 1) the 15 scheduled MBF/CBC collections at the clinic and 2) the 13 monthly field worker home visits (see Exhibit 7 and Section 7.2), “Detailed Description of Study Stages and Visits”). All these scheduled sample collections and home visits will be undertaken whether or not children are symptomatic, and will include checks of temperature. All children known to be parasitemic with symptoms, including those with fever (≥ 37.5C) or history of fever will be documented as such and treated as medically appropriate on the same day. The malaria blood films (MBFs) of children who are afebrile and well at the clinic will be read according to a time schedule dictated by microscopist workload. Therefore, any asymptomatic, but parasitemic, children who do not have their MBFs read “in real time” will not receive antimalarial treatment. (It is anticipated that these will represent 80-90% of children during high-transmission months). During field worker visits to the subjects’ homes, any child found to be ill from any cause will be promptly transported by the field worker to the WRP KC for evaluation and appropriate medical management.

*Passive case detection* is represented by subjects’ accessibility to the 12 field stations, which are manned on a 24-hour basis by field workers, as described in Section 16.3.3. Passive case detection will be in effect from the day of screening to Study Day 0 (for all those screened), and from Study Day 0 to study end (for all those enrolled). Parents of subjects will be advised on a continuous basis to bring any ill subject to a field station for immediate transportation to the KC at any time, night or day. Field workers will have standing instructions to arrange transport to the KC for any subject with reported fever or history of fever in the past 24 hours. Thus, all such children will be evaluated with an acute MBF and CBC. Subjects will then be treated at the KC IAW Section 7.3.3 (for malaria), Section 6.3.1 (for other illnesses), clinic SOPs, and established clinic guidelines. (This facility and its staffing are described in detail in Section 7.3.)

At study start, parents will be advised to seek medical attention for subjects *only* from the WRP KC. The exception of emergency medical care when remote from Kombewa Division will be fully explained to the parents. If a subject receives medical attention elsewhere, the investigators will attempt to obtain copies of any medical records and will encourage the parent/guardian to seek care for the subject only from the study physicians in the future.

Procedures for identification of subjects upon arrival at WRP KC are described in SSPs No. MAL 036-02 and MAL 036-04.

### Field Workers: Activities and Competencies

Field workers will have undergone a 2- to 3-week training period during which they will be taught basic study procedures such as taking vital signs and collecting finger stick blood samples. They will be given additional didactic information regarding malaria and other general health concerns. At the end of this period, they will have been tested on their knowledge and skills. Only those who satisfactorily pass this test will participate in the study.

Throughout the study period, field workers will man 12 satellite field stations 24 hours a day, 7 days a week. These stations will be located within a one-mile radius of parents/subjects and will provide a point of contact with the WRP KC by way of a hand-held radio or cellular phone. These field stations are not intended to be “aid stations”; they will be capable of rendering only the most basic first aid measures prior to transport of a patient/subject to the WRP KC. If an ill subject is brought to a field station, the field worker on duty will be able to arrange transport to the WRP KC.

Throughout the study period, field workers will conduct monthly home visits to determine the location of parents/subjects and remind parents of scheduled visits. Field workers will perform their 13 monthly home visits in order to identify malaria cases.

Field worker supervisors will visit a sample of subjects periodically to ensure that field workers are indeed tracking and collecting the required information (IAW SOP No. 101.01: Fieldworker Evaluation).

### Study Follow-up Periods

The solicited AE follow-up periods are the seven days following each vaccination (vaccination day and post-vaccination days 1, 2, 3, and 6). The unsolicited AE follow-up periods run for 30 days (vaccination days and the subsequent 29 days). SAE reporting will continue throughout the duration of the study (12 months). During the EFP all SAEs must be reported to the ORP within 24 hours of occurrence if possible (see Section 10.5.2). After the conclusion of the EFP, SAEs will be reported within 30 days from the time of occurrence except for deaths or events judged to be causally related to vaccine administration, which must be reported within 24 hours. In the event that a child is treated outside the WRP KC or the NNPGH, copies of all available clinical records of the encounter will be obtained and placed in the subject’s record. If a study subject is admitted to NNPGH, a member of the clinical team will visit the subject at least once daily and report to the PI or designee. The PI will be in contact with the pediatrician providing care to the subject and will ensure that the locally appropriate medical care is provided.

The efficacy follow-up period (EFP: surveillance for clinical malaria cases, parasite densities, and immunogenicity measurement) runs from study day 71 (fourteen days after the third vaccine dose) until Study Day 240(i.e., for 6 months).

The addendum efficacy follow-up period (AEFP: surveillance the same parameters as for the EFP) commences with the end of the EFP and continues until Study Day 364 (i.e., for 4 months).

Both the FESDR and the AESDR will include separate sections on intention-to-treat (ITT) analysis, which will reflect efficacy surveillance data beginning at the first vaccination (SD 0).

On study day 57 (the third vaccine dose), a period of twice monthly subject visits commences. These follow-up visits consist of monthly field worker home visits alternating with monthly WRP KC visits, such that surveillance visits of one kind or another occur every two weeks.

Exhibit 5. Mal-036 AE, SAE and 2 Efficacy Follow-up (F/U) Periods

| **Month** | **1** | | **2** | **3** | | **4** | | **5** | | **6** | **7** | | **8** | **9** | | | **10** | **11** | **12** |
| --- | --- | --- | --- | --- | --- | --- | --- | --- | --- | --- | --- | --- | --- | --- | --- | --- | --- | --- | --- |
| Study Day | 0-30 | | 31-60 | 61-90 | | 91-120 | | 121-150 | | 151-180 | 181-210 | | 211-240 | 241-270 | | | 271-300 | 301-330 | 331-364 |
|  | V | | V | V | |  | |  | |  |  | |  |  | | |  |  |  |
| F/U Period for Unsolicited AEs | | | | | |  |  | |  |  | |  |  | | |  |  |  |
| SAE F/U Period (ITT follow-up period) | | | | | | | | | | | | | | | | | | |
|  |  | | | Efficacy Follow-up Period (EFP)*  (Fully double-blinded) | | | | | | | | | |  |  | |  |  |
|  |  | |  | |  | | |  |  |  |  | | | Addendum EFP*  (Partially unblinded) | | | | |
| Monthly Field Worker Home Visits  (Staggered against monthly WRP KC Visits) | | | | | | | | | | | | | | | | | | |
|  |  | | Monthly WRP KC Visits  (Staggered against monthly FW Visits) | | | | | | | | | | | | | | | |
| ITT Analysis Period  (Passive Case Detection) | | | | | | | | | | | | | | | | | | |

V = 7 day F/U for Solicited AEs following each vaccination

* For malaria cases, parasite densities, genotyping and immunogenicity

## Detailed Description of Study Stages and Visits

The following schedule shows the visits for a single subject. Each event/day indicated on this schedule reflects a range of 7-10 days (or up to 25 days if the desired number of subjects has not been reached by the 10th day) during which these events occur for the entire study population. Any death, out-migration, absence from Kombewa, and antimalarial usage will be elicited and documented for every scheduled clinic or home visit from Study Day 0.

**Days –45 to 0** **Screening of Subjects**

***Visit 1***

- Verification of written Informed Parental Consent
- Assignment of Subject Identification (SID) number
- Record axillary temperature, blood pressure, pulse, respirations
- Provision of medical history by subject’s parent/guardian
- Health assessment and physical examination (includes physical exam of all major body systems: ENT, pulmonary, cardiovascular, musculoskeletal, central nervous, renal, gastrointestinal and skin). Abnormal findings will be recorded in the subject’s record.
- Check of all inclusion and exclusion criteria
- Check weight
- Collect 2 ml venous blood sample for measurement of:
- Complete blood count (CBC), creatinine, ALT
- MBF
- Sickle cell, G6PD deficiency, and alpha-thalassemia
- 3D7 allotyping
- Provide each parent with SID card containing subject’s unique study number and parent/subject photograph. The photograph will be taken only of eligible (pending laboratory results) subjects who agree to participate and have been consented. It may be taken on any day within this period prior to the first vaccination

**Day 0 Enrollment, Randomization, and Vaccination 1**

***Visit 2***

Before vaccination:

- Check subject’s SID card to confirm identity
- Record axillary temperature, blood pressure, pulse, respirations
- Review screening laboratory test results
- Review inclusion/exclusion criteria and check of contraindications/ precautions
- Record any parental or subject complaints, interim history, history-directed physical examination and examination of the immunization leg for any abnormalities
- Review concomitant medications
- Record baseline data for solicited general symptoms
- Collect 3 ml of whole venous blood for the measurement of:
- CBC, creatinine, ALT
- Serum for anti-MSP-1 antibody titer
- 3D7 allotyping
- MBF
- Enrollment/Randomization
- Confirm that the subject’s randomization number and SID number agree with label on syringe
- Administer study vaccine dose 1; record site, date and time of injection.

After vaccination:

- Observe for 60 minutes.
- Record blood pressure, pulse, axillary temperature at the end of 60 minute observation period
- Record site of injection examination
- Record solicited and unsolicited AEs
- Instruct parent(s) to return with subject to WRP Kombewa Clinic immediately should subject manifest any sign or symptom perceived as serious.

**Days 1-3 Daily Post- vaccination 1 follow-up visits**

***Visits 3-5***

- Record pulse, axillary temperature
- Examine site of injection
- Record solicited and unsolicited AEs
- History-directed general physical examination
- Check concomitant medications

**Day 6 ± 3 Day 6 Post- vaccination 1 follow-up visit**

***Visit 6***

- Record pulse, axillary temperature
- Examine site of injection
- Record solicited and unsolicited AEs
- History-directed general physical examination
- Check concomitant medications

**Day 29  9 days Vaccination 2**

***Visit 7*** Before vaccination:

- Check SID card to confirm subject identity
- Confirm that vaccination dose 1 was administered
- Record axillary temperature [must be <37.5 C], blood pressure, pulse, respirations
- Review inclusion/exclusion criteria and check of contraindications/ precautions
- Review day 0 laboratory test results
- Record any parental or subject complaints, interim history, history-directed physical examination and examination of the immunization leg for any abnormalities
- Review concomitant medications
- Record baseline data for solicited general symptoms.
- Collect 3 ml of whole venous blood for the measurement of:
- CBC, creatinine, ALT
- Serum for anti-MSP-1 antibody titer
- 3D7 allotyping
- MBF
- Confirm that the subject’s randomization number and SID number agree with label on syringe
- Administer study vaccine dose 2; record site, date and time of injection.

After vaccination:

- Observe for 60 minutes.
- Record blood pressure, pulse, axillary temperature at the end of 60 minute observation period
- Record site of injection examination
- Record solicited and unsolicited AEs
- Instruct parent(s) to return with subject to WRP Kombewa Clinic immediately should subject manifest any sign or symptom perceived as serious

**Days 30-32 Daily Post-vaccination 2 follow-up visits**

***Visits 8-10***

- Record pulse, axillary temperature
- Examine site of injection
- Record solicited and unsolicited AEs
- HIstory-directed physical examination
- Check concomitant medications

**Day 35 ± 3 Day 6 Post - vaccination 2 follow-up visit**

***Visit 11***

- Record pulse, axillary temperature
- Examine site of injection
- Record solicited and unsolicited AEs
- HIstory-directed general physical examination
- Check concomitant medications

**Day 57  9 days Vaccination 3**

***Visit 12***

Before vaccination:

- Check SID card to confirm subject identity
- Confirm that vaccination dose 1 and 2 were administered
- Record axillary temperature [must be <37.5 C], blood pressure, pulse, respirations
- Review inclusion/exclusion criteria and check of contraindications/ precautions
- Review day 29 laboratory test results
- Record any parental or subject complaints, interim history, history-directed physical examination and examination of the immunization leg for any abnormalities
- Review concomitant medications
- Record baseline data for solicited general symptoms.
- Collect 3 ml of whole venous blood for the measurement of:
- CBC, creatinine, ALT
- Serum for anti-MSP-1 antibody titer
- 3D7 allotyping
- MBF
- Confirm that the subject’s randomization number and SID number agree with label on syringe
- Administer study vaccine dose 3; record site, date and time of injection.

After vaccination:

- Observe for 60 minutes.
- Record blood pressure, pulse, axillary temperature at the end of 60 minute observation period
- Record site of injection examination
- Record solicited and unsolicited AEs
- Instruct parent(s) to return with subject to WRP Kombewa Clinic immediately should subject manifest any sign or symptom perceived as serious.

**BEGIN EFFICACY FOLLOW-UP PERIOD 14 DAYS AFTER THIS VISIT.**

**Days 58-60 Daily Post-vaccination 3 follow-up visits**

***Visits 13-15***

- Record pulse, axillary temperature
- Examine site of injection
- Record solicited and unsolicited AEs
- History-directed physical examination
- Check concomitant medications

**Day 63 ± 3 Day 6 Post- vaccination 3 follow-up visit**

***Visit 16***

- Record pulse, axillary temperature
- Examine site of injection
- Record solicited and unsolicited AEs
- History-directed general physical examination
- Check concomitant medications

**Day 85  10 Day 30 Post-vaccination 3 follow-up**

***Visit 17***

- Record pulse, axillary temperature
- Interim medical history (including any history of fever in last 24 hours)
- History-directed physical examination
- Record any unsolicited adverse events occurring after the last vaccine dose
- Check concomitant medications
- Collect 3 ml of blood for determination of:
- Serum for anti-MSP-1 antibodies
- 3D7 allotyping
- CBC, creatinine, ALT
- MBF

**Days 14 to 354 ± 7 Field Worker Home Visits**

***Field Worker Visits 1-13***

- Monthly field worker home visits will fall o/a Study days 14, 43, 71, 99, 129, 158, 186, 214, 242, 270, 298, 326, and 354 (all ± 7)
- Field workers will take axillary temperatures, solicit history of fever in the last 24 hours, remind parents of appointments and reconfirm their locations
- Any subject with a fever or history of fever in the past 24 hours will be taken to the KC for evaluation, including MBF and CBC.
- Any deaths, out-migrations, absences from Kombewa, and antimalarial usage will be documented
- Parents/subjects will continue to attend the WRP KC whenever the latter are sick
- Check concomitant medications

**Days 115 to 364  14 WRP KC Visits**

***Visits 18-27***

- Monthly WRP KC visits will fall o/a Study days 115, 143, 171, 200, 228, 256, 284, 310, 340, and 364 (all ± 14)
- Beginning on study day 115, parents/subjects will visit the WRP KC monthly ± 14 days for interim history, including history of fever in 24 hours, axillary temperature, and 1 ml blood sample collection for MBF, CBC, and 3D7 allotyping
- On Study days 171, 256, and 340, an additional 1 ml of blood will be collected from which serum for anti-MSP-1 antibody titers will be aliquoted
- Check concomitant medications
- History-directed physical exam
- Parents/subjects will continue to attend the WRP KC whenever the latter are sick
- Any deaths, out-migrations, absences from Kombewa, and antimalarial usage will be documented

Exhibit 6. Intervals Between Study Visits

| **Interval** | **Size of Interval** |
| --- | --- |
| ***(Visit 1********Visit 2)***  ***(Visit 2********Visit 6)*** | ***Variable***  ***6 ± 9 days*** |
| ***(Visit 2********Visit 7)*** | ***28 ± 9 days*** |
| ***(Visit 7********Visit 11)*** | ***6 ± 9 days*** |
| ***(Visit 7********Visit 12)*** | ***28 ± 9 days*** |
| ***(Visit 12********Visit 16)*** | ***6 ± 9 days*** |
| ***(Visit 12********Visit 17)*** | ***29 ± 7 days*** |
| ***(Visit 18********Visit 27)*** | ***29 ± 7 days*** |

Exhibit 7. Schedulea of Routine Subject Evaluations

| Clinic Visit | 1 | 2 | 3-6 | 7 | 8-11 | 12 | 13-16 | 17 | 18, 19 | 20 | 21, 22 | 23 | 24, 25 | 26 | 27 | FW 1-13 |
| --- | --- | --- | --- | --- | --- | --- | --- | --- | --- | --- | --- | --- | --- | --- | --- | --- |
| **Study Day** | **Scr** | **0** | **1,2,3,6** | **29** | **30, 31, 32, 35** | **57** | **58, 59, 60, 63** | **85** | **115, 143** | **171** | **200,228** | **256** | **284, 310** | **340** | **364** | **14-354** |
| Written Informed Consent | x |  |  |  |  |  |  |  |  |  |  |  |  |  |  |  |
| Verification of Eligibility Criteria | x | x |  | x |  | x |  |  |  |  |  |  |  |  |  |  |
| Medical Historyk | x |  |  |  |  |  |  |  |  |  |  |  |  |  |  |  |
| Weight | x |  |  |  |  |  |  |  |  |  |  |  |  |  |  |  |
| Respirations | x | x |  | x |  | x |  |  |  |  |  |  |  |  |  |  |
| Assign SID | x |  |  |  |  |  |  |  |  |  |  |  |  |  |  |  |
| Check SID |  | x |  | x |  | x |  |  |  |  |  |  |  |  |  |  |
| Interim Medical History |  | x | x | x | x | x | x | x | x | x | x | x | x | x | x |  |
| Physical Examination | x |  |  |  |  |  |  |  |  |  |  |  |  |  |  |  |
| History-directed PE |  | x | x | x | x | x | x | x | x | x | x | x | x | x | x |  |
| Review labs |  | x |  | x |  | x |  | x | x | x | x | x | x | x | x |  |
| Examine injection site |  | x | x | x | x | x | x |  |  |  |  |  |  |  |  |  |
| CBCd | xb | xc |  | xc |  | xc |  | x | x | x | x | x | x | x | x | xm |
| Creatinine, ALT | xb | xc |  | xc |  | xc |  |  |  |  |  |  |  |  |  |  |
| Check Hemoglobinopathies | x |  |  |  |  |  |  |  |  |  |  |  |  |  |  |  |
| Serum for MSP-1 Ab Responses and GIA |  | xc |  | xc |  | xc |  | x |  | xe |  | xe |  | xe |  |  |
| 3D7 Allotyping | x | x |  | x |  | x |  | x | x | x | x | x | x | x | x | xm |
| Malaria Blood Film | x | x |  | x |  | x |  | x | x | x | x | x | x | x | x | xm |
| Axillary Temperature | x | x | x | x | x | x | x | x | x | x | x | x | x | x | x | x |
| Blood Pressure | x | xf |  | xf |  | xf |  |  |  |  |  |  |  |  |  |  |
| Pulse | x | x | x |  | x |  | x | x |  |  |  |  |  |  |  |  |
| Study Vaccine Administration |  | x |  | x |  | x |  |  |  |  |  |  |  |  |  |  |
| Check Contraindications / Precautions |  | x |  | x |  | x |  |  |  |  |  |  |  |  |  |  |
| Assess Adverse Eventsg |  | x | x | x | x | x | x | x |  |  |  |  |  |  |  |  |
| *(continued)* | | | | | | | | | | | | | | | | |

Exhibit 7. Schedulea of Routine Subject Evaluations (continued)

| Clinic Visit | 1 | 2 | 3-6 | 7 | 8-11 | 12 | 13-16 | 17 | 18, 19 | 20 | 21, 22, | 23 | 24, 25 | 26 | 27 | FW 1-13 |
| --- | --- | --- | --- | --- | --- | --- | --- | --- | --- | --- | --- | --- | --- | --- | --- | --- |
| **Study Day** | **Scr** | **0** | **1,2,3,6** | **29** | **30, 31, 32, 35** | **57** | **58, 59, 60, 63** | **85** | **115, 143** | **171** | **200,228** | **256** | **284, 310** | **340** | **364** | **14-354** |
| Assess Serious Adverse Events |  | x | x | x | x | x | x | x | x | x | x | x | x | x | x | x |
| Concomitant Medicationsh | x | x | x | x | x | x | x | x | x | x | x | x | x | x | x | x |
| Monthly FW home visitsi |  |  |  |  |  |  |  |  |  |  |  |  |  |  |  | x |
| Hx fever in previous 24 hrs |  |  |  |  |  |  |  | x | x | x | x | x | x | x | x | x |
| Monthly WRP KC visits |  |  |  |  |  |  |  |  | x | x | x | x | x | x | x |  |
| Record baseline covariatesn | x |  |  |  |  |  |  |  |  |  |  |  |  |  |  |  |
| Exposure time variablesl |  | x | x | x | x | x | x | x | x | x | x | x | x | x | x | x |
| Scheduled blood volumes (ml) | 2 | 3 | 0 | 3 | 0 | 3 | 0 | 3 | 1 | 2 | 1 | 2 | 1 | 2 | 1 | 0 |
| **Cumulative** Blood Vol. (ml) | 2 | 5 | 5 | 8 | 8 | 11 | 11 | 14 | 16 | 18 | 20 | 22 | 24 | 26 | 27j |  |

1. Days/dates for doses 2 and 3 are for planning purposes and are provisional only.
2. Performed within 45 days prior to randomization.
3. Blood collected just before immunization.
4. Limited to Hgb, WBC, RBC, lymphocytes, platelets.
5. Serum for MSP-1 antibodies collected on Study Days 171, 256, and 340.
6. Pre-dose and 60 min after each dose.
7. Solicited symptoms collected on Study Days 0, 1, 2, 3, and 6 after each dose. Unsolicited AEs collected from SD 0 through 85.
8. Concomitant medications collected from Study day -7 through 364.
9. Monthly field worker visits to checkaxillary temps, history of fever, and location and general status of subjects.
10. Volume does not include that taken for repeat screenings (if necessary) or for diagnostic samples in case of illness.
11. Includes history of malaria prevention methods used by the subject.
12. Includes death, out-migration, absences from Kombewa, and antimalarial drug usage.
13. Collected if temp ≥ 37.5°C, or if history of fever in previous 24 hours.
14. Age, sex, bed net use, nearest field site station, Hgb genotype.

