# STUDY DESIGN and METHODOLOGY

## Overview

- Double-blind, randomized, controlled, phase IIb (pilot efficacy) field trial of a candidate antigen/adjuvant
- One study center, with 12 outlying (satellite) field stations
- Screening will be performed no more than 45 days prior to the first inoculation
- 400 subjects will be randomized 1:1 between two arms (FMP1/AS02A and rabies vaccine)
- Immunization schedule will be 0, 1, and 2 months for both study arms
- The four-week intervals between doses may be extended for up to two additional weeks if *temporary suspension* (see Section 6.9.1) is deemed advisable because of SAEs or other concerns
- All subjects will be randomized on the day of first vaccination
- Route of inoculation will be by IM injection into the left anterolateral thigh muscle (unless compelling reason for an alternate injection site is evident)
- Study duration will be approximately about 14 months per subject
- Seven-day follow-up period for solicited adverse events (five visits: vaccination day plus post-vaccination days 1, 2, 3, and 6)
- Thirty day follow-up period for unsolicited adverse events (vaccination day plus 29 subsequent days)
- Follow-up of serious adverse events (SAEs) for study duration
- Efficacy Follow-up Period (EFP): Starting 14 days after the third vaccination (Study Day 71), active case detection commences with visits approximately every 28 days to the WRP Kombewa clinic and terminates after six months (o/a Study Day 240): EFP = 169 days = six (28 day) months
- The primary study analysis for all endpoints will be done on the cleaned EFP database after a data-lock-point
- Addendum Efficacy Follow-up Period (AEFP): Starting with the end of the EFP (o/a Study Day 240), active case detection commences with visits approximately every 28 days to the WRP Kombewa clinic and terminates after 10 months (o/a Study Day 364); AEFP = 125 days = four and a half (28 day) months. This portion of the trial is partially unblinded.
- The study addendum analysis for all endpoints will be done on the AEFP database after a data-lock-point
- Malaria cases will be detected by active and passive means
- Active case detection will be through scheduled, facilitated visits by participants to the Kombewa clinic and scheduled, field worker visits to participants’ homes
- Passive case detection will take place by unscheduled, self-presentation of participants to the Kombewa Clinic

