### Vaccination Process

On each vaccination day, criteria for continued eligibility will be reviewed and reverified. A history-directed physical examination will be done and axillary temperature, pulse, blood pressure, respirations and baseline general symptom history will be recorded. Venous blood will be collected for laboratory analysis as detailed in Section 8.1.

After the identity of the subject is checked (by comparing the SID number and photograph in subject’s record with the parent/subject’s photo ID), subjects will be vaccinated by intramuscular injection into the left anterolateral thigh muscles unless a compelling reason for using the right anterolateral thigh is evident (See also SSP No. MAL036-04: Vaccination Day Procedures). All vaccinations will be done in a fashion that maintains double-blinding (See Section 9.5.1). The vaccination periods may be up to ten consecutive days, but every effort will be made to vaccinate all 400 children over seven days.

Although all the foregoing study days are provisional (circumstances may require delays of up to two weeks), vaccinations (200 test article recipients, 200 rabies vaccine recipients) will occur on or about Study Days 0 (Dose 1), 29 (Dose 2), and 57 (Dose 3).

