### Surveillance Period for Occurrence of Adverse Events

All AEs occurring within one month (maximum 30 days) following administration of each dose of vaccine must be recorded on the Adverse Event CRF, irrespective of severity or likelihood of vaccination-relatedness.

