### Secondary Endpoints

Because this is a Phase IIb trial, it has many secondary endpoints. Their purpose is to gain insight into the efficacy of the vaccine and to help define a primary endpoint for a confirmatory Phase III trial. They are not intended for use to make formal claims about the vaccine.

Measurements of efficacy during the EFP:

- Times to clinical episode of *P. falciparum* malaria meeting the various secondary case definitions shown in Exhibit 8
- Time to presence of asexual stage *P. falciparum* parasites during the six-month efficacy follow-up period
- Time to parasite density  50,000 asexual stage *P. falciparum* parasites per microliter of blood during the six-month efficacy follow-up period
- Number of clinical episodes of malaria, per subject, meeting the primary case definition
- Presence of MSP-1 3D7 parasites in clinical cases of malaria meeting the primary case definition
- Presence of MSP-1 3D7 parasites at a given cross-section survey time
- Time to anemia defined as Hgb < 8.0 g/dl, whether by active or passive case detection
- Proportion of subjects with anemia (Hgb < 8.0 g/dl)

Safety during the EFP:

- Occurrences of solicited AEs during a seven‑day follow-up period (vaccination day and six subsequent days) after each vaccination (five visits: vaccination day and days 1, 2, 3, and 6)
- Occurrences of unsolicited AEs during a 30-day follow-up period after each vaccination (vaccination day and 29 subsequent days)
- Occurrences of SAEs between the first vaccination and the end of the EFP

Immunogenicity during the EFP:

- Geometric means of MSP-1 Ab titers at Visits 2, 7, 12, 17, 20, and 23 (o/a Study Days 0, 29, 57, 85, 171, and 256)

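### The Exhibit 7 footnote ends unsolicited AE collection at SD 85, which does not match the 30-day window after dose 3, and Visit 17 may take place before that window closes

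*Protocol*

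**What the plan says.** **Window length.** Section 12.1.2 defines the endpoint over a "30-day follow-up period after each vaccination", spelled out as the vaccination day and the next 29 days. Sections 6.1, 7.1.6 and 10.1.3 use the same count. Section 10.1.2 makes recording mandatory: "All AEs occurring within one month (maximum 30 days) following administration of each dose of vaccine must be recorded".

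**End of collection.** The Exhibit 7 footnote on adverse events states: "Unsolicited AEs collected from SD 0 through 85".

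**Closing visit.** Visit 17 sits on nominal Day 85 with a tolerance of 10 in Section 7.2 and is labelled as day 30 after the third vaccination. Its task is: "Record any unsolicited adverse events occurring after the last vaccine dose". Exhibit 6 places the same visit 29 ± 7 days after Visit 12, the dose 3 visit. In Exhibit 7 the general AE row is empty after Visit 17 and in the field worker column; only serious AEs continue.

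**Timing of dose 3.** It is planned for about SD 57, with a tolerance of nine days in Sections 6.8 and 7.2. Section 7.1.2 adds that "circumstances may require delays of up to two weeks". Section 6.1, on temporary suspension, says: "The four-week intervals between doses may be extended for up to two additional weeks".

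**The concern.** The endpoint runs from the dose; the footnote runs on the study calendar. The two agree only if dose 3 is given before SD 57. The window is already cut for a child dosed on time, and a late dose 3 shortens it further if SD 85 is kept.

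Doses 1 and 2 are not exposed in this way. Their nominal windows end on SD 29 and SD 58, and scheduled AE assessments continue past both days. Only dose 3 has no scheduled AE assessment behind it. At stake is the absolute 30-day unsolicited AE rate after the last dose, and whether it can be set beside the rates after doses 1 and 2. Children dosed late, because of illness or a safety suspension, would be the least completely followed.

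**Working it through.** **Inputs.** Window: vaccination day plus 29 days, 30 days inclusive (Section 12.1.2). Dose 3: SD 57 nominal; SD 66 at the nine-day limit (57 + 9); SD 71 after one two-week delay (57 + 14); SD 74 if both Exhibit 6 dose intervals run to their limit (28 + 9 + 28 + 9). Footnote end: SD 85.

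**Step 1: the plan's own figure.** Window end = dose day + 29 = 57 + 29 = SD 86. The footnote's SD 85 is not reproduced; it is one day short. SD 85 is 28 days after SD 57, whereas Exhibit 6 puts Visit 17 at 29 days, also SD 86.

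**Step 2: SD 85 as a hard stop.** Days captured = min(dose day + 29, 85) − dose day + 1.

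| Dose 3 | Window ends | Captured | Lost |
|---|---|---|---|
| SD 57 | SD 86 | 29 | 1 (3%) |
| SD 66 | SD 95 | 20 | 10 (33%) |
| SD 71 | SD 100 | 15 | 15 (50%) |
| SD 74 | SD 103 | 12 | 18 (60%) |

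**Step 3: SD 85 as the nominal day of Visit 17, moving with dose 3.** Exhibit 6 allows 29 − 7 = day 22 to 29 + 7 = day 36 after dose 3. Days captured = min(30, visit day + 1).

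- Visit on day 22: 23 captured, 7 lost (7/30 = 23%).
- Visit on day 29 or later: 30 captured, 0 lost.

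This result is the same whether or not dose 3 was late.

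**Step 4: the two windows for Visit 17.** Section 7.2, with its days held as printed, gives 85 ± 10 = SD 75 to 95. Exhibit 6 gives dose day + 22 to dose day + 36.

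| Dose 3 | Exhibit 6 | Section 7.2 |
|---|---|---|
| SD 57 | SD 79–93 | SD 75–95 |
| SD 66 | SD 88–102 | SD 75–95 |
| SD 71 | SD 93–107 | SD 75–95 |

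The windows differ even for an on-time dose. For a dose on SD 71 they share only SD 93–95, which is days 22 to 24, so a visit that satisfies both always falls before day 29.

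**The case against.** The strongest reply is that SD 85 is only the column heading of Visit 17. The first footnote of Exhibit 7 calls the days for doses 2 and 3 provisional, and the clause in Section 7.1.2 that allows delays describes the study days in the same way. Moving dose 3 under that clause while holding SD 85 still is selective. Under Exhibit 6, a dose on SD 66 or SD 71 carries Visit 17 to SD 95 or SD 100, exactly day 29. The visit's task is also tied to the last dose, and Section 10.1.2 is mandatory. This stands: a reader might infer from the footnote that a third or half of the window is lost in late-dosed children, but the documents do not establish SD 85 as a fixed stop that overrides the dose-based rules. Half would not be the maximum in any case, as the SD 74 row shows.

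A reader might also pair a dose on SD 66 with a visit on SD 75 and conclude that follow-up could end 9 days after dose 3. That breaks the 22-day minimum in Exhibit 6. It shows that the two windows conflict, not that such follow-up is permitted.

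Second, Section 10.1.3 requires undocumented AEs to be recorded at every visit or encounter, and sick children come to the study clinic. Some late events will therefore be caught. This stands in part: the rule exists, but Exhibit 7 schedules no general AE assessment after Visit 17, and the listed field worker tasks contain no AE question. The last days would rest on a general rule that the schedule does not carry out.

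Third, both arms follow the same blinded schedule and serious AEs are followed throughout. This stands in full.

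**Conclusion.** The inconsistency is real and modest. The footnote contradicts the 30-day window by one day for a dose on SD 57. The larger losses, 10 of 30 days at SD 66 and 15 of 30 at SD 71, follow only if the footnote is applied literally over the dose-anchored text. On the reading that best fits the whole protocol, up to 7 of the 30 days after dose 3 can fall after the last scheduled AE assessment, in any child whose Visit 17 is early under Exhibit 6.

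These are days of observation, not events. At a constant event rate, 7 days would carry 23% of a child's events, before any recovery through Section 10.1.3. The documents give neither the timing of events nor the share of early visits, so the overall under-count cannot be stated. A reader might infer that the vaccine comparison is biased or that the endpoint is not delivered; neither follows. The absolute dose 3 rate may be too low, and less comparable with doses 1 and 2. The primary endpoint and the sample size are untouched.

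**What to change.** 1. In the Exhibit 7 footnote, replace SD 0 through 85 with: *through day 29 after each dose, counted from the actual vaccination date (vaccination day = day 0)*.
2. Reconcile the Visit 17 label, the Section 7.2 tolerance and the Exhibit 6 interval into one window anchored to the actual date of dose 3.
3. Where Visit 17 falls before day 29, mark an unsolicited AE assessment in Exhibit 7 at the next existing contact on or after that day: the field worker visit at about SD 99 or the clinic visit at about SD 115.

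The cost is a wording change and one extra AE question for some children. No visit is added.
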